**SUMMARY**

**Rationale:** The laparoscopic adrenalectomy is the standard of care for benign adrenal tumors. Several modifications and refinements of the surgical technique have been described to improve patients recovery and lower the number of complications, such as the retroperitoneoscopic technique^[[1]](#endnote-1)^. However, 10% of our patients that received a retroperitoneoscopic adrenalectomy report (temporary) pain and 21% (temporary) dullness in the lumbar region, which can be a result of damage to the subcostal nerves (non-published data). We aim to see if the subcostal nerve can be visualized pre- and postoperatively by ultrasound, what the distances are from nerve to trocar locations, and if we can visualise nerve injuries. If so, we aim to see in the future if the surgical technique can be improved to prevent this.

**Objective**: to identify the subcostal nerve in retroperitoneoscopic adrenalectomies and to evaluate perioperative nerve damage

**Study design:** single-centre, prospective cohort study

**Study population:** all patients who undergo a retroperitoneoscopic adrenalectomy, except patients with Cushing syndrome

**Main study parameters/endpoints:**

*Primary objectives:*

- To assess postoperative nerve damage on ultrasound.
- To measure the distances of the subcostal nerve to trocar positions.

*Secondary outcomes:*

- To identify postoperative cutaneous hyperesthesia or hypoesthesia:
- To correlate postoperative dullness, neuropathy, pain or muscle weakness to subcostal nerve damage on ultrasound.

**Nature and extent of the burden and risks associated with participation, benefit and group relatedness:** there are no risks. The burden for the patients is small, due to a longer narcosis (estimated 10 minutes) and extra examinations (ultrasound, physical examination, questionnaire) after 6 weeks.

**INTRODUCTION AND RATIONALE**

In 1992 the first transabominal laparoscopic adrenalectomy (TLA) was described by Gagner et al^[[2]](#endnote-2)^. Compared to the open technique, TLA has advantages with lower morbidity and complication rates, decreased blood loss, less postoperative pain, shorter hospital stay, and improved cosmetic effect^[[3]](#endnote-3)^. Therefore, TLA has become the standard of care for the management of benign adrenal tumors, and in selected cases in the treatment of small malignant adrenal tumors. In 1994 the retroperitoneoscopic adrenalectomy (PRA) was described as an alternative route to the adrenal gland, which allows a more direct access with a minimal dissection of the surrounding structures^[[4]](#endnote-4)^. Already in literature this technique shows excellent results regarding operating times, blood loss, postoperative pain and recovery after surgery^[[5]](#endnote-5)^ ^[[6]](#endnote-6)^.

TLA was introduced in our hospital in 1993. Because of an increase in referred patients, PRA was introduced in our hospital in 2011 for its potential benefits in shorter operating times, less pain, quicker recovery and shorter hospital stay. From 2011, patients were eligible for PRA with a body mass index (BMI) of <35 kg/m2, with a tumor diameter <7 cm, and with low suspicion of malignancy. Otherwise, TLA or open adrenalectomy were performed, for these techniques provide more working space and more landmarks during surgery.

While the rate of postoperative complications after PRA is low, still 10% of our patients report (temporary) pain and 21% (temporary) dullness in the lumbar region, which can be a result of damage to the subcostal nerves. In some cases this is temporary, but in other cases this can be permanent, consequently resulting in a lower quality of life. Our hypothesis is that these symptoms can be the result of damage to the inter- or subcostal nerves (lateral and medial cutaneous branches).

In literature neuropathy is a common symptom after surgery. The affected nerve and resulting neuropathy, muscle weakness or pain depends on different types of surgery. Common mechanisms of surgery related nerve injuries include compression, entrapment/angulation, direct trauma including crushing or laceration injuries, and indirect trauma^[[7]](#endnote-7)^. Walz et al. shows a prevalence of chronic hypoesthesia of the abdominal wall of 8% after retroperitoneoscopic adrenalectomy for primary adrenal tumors, although because of the retrospective character of this study there could be a selection bias in these data^[[8]](#endnote-8)^. After percutaneous nephrolithotomy sensory neurological complications were reported in 12% of the patients, with a significant correlation between prolonged duration of surgery and the incidence of sensory complications^[[9]](#endnote-9)^. After living-donor nephrectomies the incidence of chronic postoperative pain was 5.7%, resulting in a significant lower quality of life^[[10]](#endnote-10)^. Depending on the type of surgery, chronic postsurgical pain is often neuropathic pain (on average 30% of cases with a range from 6% to 54% and more)^[[11]](#endnote-11)^. Pain including such a neuropathic component is usually more severe than nociceptive pain and often affects the quality of life more adversely.

Since the introduction of PRA, several modifications and refinements of the surgical technique have been implemented to improve patients’ recovery and lower the number of intra- and postoperative complications. Because nerve damage can result in significant complaints and this subsequently can result in a lower quality of life, we aim to see if the surgical technique can be further improved by locating this nerve and prevent damage. Therefore, we plan to investigate if the intercostal and subcostal nerves can be visualized pre- and postoperatively by ultrasound, what the distance is of the trocar positions to this nerve, and if we can visualise nerve injuries by ultrasound (direct lesions, oedema). Furthermore, after 6 weeks we want to repeat the ultrasound to see if nerve damage can be visualized at a later stage. If so, we aim to see in the future if the surgical technique can be altered to prevent this.

# OBJECTIVES

*Primary Objective:* to investigate if the subcostal nerve can be visualized perioperatively in patients undergoing retroperitoneoscopic adrenalectomy, to measure distance from the trocar incisions and to assess nerve damage directly postoperative.

*Secondary Objective(s):*

To identify postoperative cutaneous hyperesthesia or hypoesthesia and to correlate postoperative dullness, neuropathy, pain or muscle weakness to subcostal nerve damage on ultrasound, after 6 weeks.

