# STUDY DESIGN

A explorative single-center prospective cohort study (n=25) at the Radboud University Medical Centre in Nijmegen.

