### Baseline parameters

- Date of surgery
- Sex
- Age
- Height
- Weight
- BMI
- Comorbidity
- Medications
- Side of adrenalectomy
- Indication of surgery
- Pressure of pneumo-retroperitoneum
- Duration of surgery
- Intraoperative analgesics
- Postoperative analgesics
- Complications related to PRA
- Length of hospital stay after PRA

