## Study procedures

All patients will be approached at the outpatient clinic by [name] (researcher) after the decision is made to perform PRA, explaining the study and its procedures. They will be given additional written information including a consent form. If the patient gives informed consent and has no exclusion criteria, he/she will be included in the trial.

Preoperatively:

1. Preoperative questionnaires: (cross-sectional), duration: in total ± 15 minutes.

- Mc Gill Pain questionnaire (Dutch Language version) (5 minutes)
- Hypoesthesia questionnaire (5 minutes)
- Pain Catastrophizing Scale questionnaire (5 minutes)
- Physical examination (5 minutes)

Intraoperatively:

1. After positioning in jack-knife position, an ultrasound is performed by a clinical neurophysiology research technician with measurement of the intercostal / subcostal nerve (see scan-protocol below). Nerve locations are captured with photography. Since the objective of this explorative study is to identify nerve damage after trocar placement and surgery and to see if the current surgical technique needs improving, surgeon is blinded for the results of preoperative ultrasound measurements to reduce bias.

2. PRA will be performed using the normal, clinically and scientifically validated surgical technique.

3. After wound closure a tegaderm foil is applied over the wound. Then repeat measurement of intercostal / subcostal nerve is performed to assess nerve damage / oedema. The distance of subcostal nerves to trocar locations (shortest distance to nerve, in mm) is measured. Again this is captured with photography. Surgeon is blinded for these results as well to prevent bias in future procedures. After this a sterile drape is applied.

Postoperatively after 6 weeks:

1. Postoperative questionnaires: (cross sectional), duration: in total ± 15 minutes.

- Mc Gill Pain questionnaire (Dutch Language version) (5 minutes)
- Hypoesthesia questionnaire (5 minutes)

2. Physical exam by clinical neurophysiology research technician to evaluate dermatomas and subtle neurological injury

3. Repeat ultrasound measurement of intercostal / subcostal nerve to assess nerve damage if neurological injury is present.

Ultrasound protocol:

- Equipment: Sonoside Xporte ultrasound system with linear 5-16Mhz probe, using preset “zenuwecho S”.

- Positioning of patient: jack-knife (see image below)

[figure not shown]

- Scan-protocol:

- Depth: 6cm, gain 60-70%

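### After surgery, symptoms are measured with the study instruments only at 6 weeks, so temporary symptoms are not systematically captured and cannot be related properly to the wound-closure ultrasound

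*Protocol*

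**What the plan says.** - **Motivation.** The Summary says that 10% of the hospital's patients "report (temporary) pain and 21% (temporary) dullness in the lumbar region". The Introduction repeats these rates, says that some cases resolve and others can be permanent, and puts forward inter- or subcostal nerve damage as the explanation.
- **Damage scan.** The primary objective in section 2 includes "to assess nerve damage directly postoperative". Section 5.3 carries this out in theatre after wound closure: "Then repeat measurement of intercostal / subcostal nerve is performed to assess nerve damage / oedema".
- **Symptom assessment.** Questionnaires and a physical examination are done before surgery. After surgery, the McGill and Hypoesthesia questionnaires appear only under the heading "Postoperatively after 6 weeks", together with "Physical exam by clinical neurophysiology research technician to evaluate dermatomas and subtle neurological injury". Nothing is scheduled at discharge or in between, although section 5.2.1 records "Length of hospital stay after PRA".
- **Correlation.** Section 2 sets the aim "to correlate postoperative dullness, neuropathy, pain or muscle weakness to subcostal nerve damage on ultrasound, after 6 weeks". It does not say whether the wound-closure scan or a 6-week scan is meant.
- **6-week scan.** The Introduction and section 5.2 plan it without condition. Section 5.3 does it only where neurological injury is found.

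**The concern.** The hypothesis covers symptoms that may be short-lived, and the scan that every patient receives is taken at the moment of injury. The first structured look at symptoms after surgery comes six weeks later. A patient with oedema on the scan and three weeks of numbness can reach the 6-week visit with nothing to report.

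If the wound-closure scan is then set against the week-6 findings, that patient looks like a false-positive scan. A weak association could be read as ultrasound failing to detect symptomatic injury when the cause is the gap between the two measurements. Analysis cannot repair this, because the early symptom status was not collected with a study instrument.

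**Working it through.** The protocol gives no power, effect size or derivation for n = 25, so there is no figure of its own to reproduce. The check compares the schedule with the objectives and then illustrates the possible size.

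**Step 1: possible pairings of scan and symptoms**

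| Scan used | Who is scanned | Consequence |
|---|---|---|
| Wound closure, against week-6 symptoms | Everyone | Comparison group exists, but there is a six-week gap; recovered patients are scan-positive, symptom-negative |
| Week 6, as in section 5.3 | Only those with neurological injury | Times match, but there is no symptom-free comparison group |
| Week 6, as in the Introduction and 5.2 | Everyone | Times match, but symptoms that have resolved are still missed |

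None of the three relates the immediate scan to early symptoms.

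**Step 2: expected numbers**

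Inputs: n = 25 (section 3); dullness 21% and pain 10% (Summary, Introduction). Expected with dullness: 25 × 0.21 = 5.25. Expected with pain: 25 × 0.10 = 2.5. Both include temporary cases.

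The share f that resolves before week 6 is not given, so it is varied as an assumption. Missed = 5.25 × f. Left = 5.25 × (1 − f). The chance of seeing no dullness at all at week 6 is (1 − 0.21 × (1 − f))^25.

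| f (assumed) | Missed | Left at week 6 | Chance of none at week 6 |
|---|---|---|---|
| 25% | 1.3 | 3.9 | 1% |
| 50% | 2.6 | 2.6 | 6% |
| 75% | 3.9 | 1.3 | 26% |

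**Step 3: effect on the association, first pairing only**

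Assume that 5 of 25 are scan-positive at wound closure, that exactly those 5 have early symptoms, and that k of them still have symptoms at week 6. The table is k and 5 − k among scan-positives, 0 and 20 among scan-negatives.

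phi = (ad − bc) / √[(a+b)(c+d)(a+c)(b+d)] = 20k / √[5 × 20 × k × (25 − k)]

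| k | Calculation | phi | Scan-positives with symptoms at week 6 |
|---|---|---|---|
| 5 | 100/√10000 | 1.00 | 100% |
| 3 | 60/√6600 | 0.74 | 60% |
| 2 | 40/√4600 | 0.59 | 40% |
| 1 | 20/√2400 | 0.41 | 20% |

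The perfect early agreement and the values of k are invented to show the direction and rough scale. They are not estimates for this trial.

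**The case against.** **Early symptoms are not wholly unrecorded.** A reader might infer that temporary symptoms are never recorded. Section 6.2.1 records adverse events that are reported spontaneously or observed, section 6.3 follows them until they abate or stabilise, and section 5.2.1 collects complications and postoperative analgesics. That stands, so the claim must be limited to systematic capture. These routes use no study instrument, mild numbness is easily left unmentioned, and silence is not a reliable negative for a correlation.

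**The pairing is not fixed.** A reader might also infer that true injuries necessarily count as symptom-free. The objective is dated at 6 weeks, and the Introduction and section 5.2 plan a 6-week scan without condition; on that reading the times match. This stands too: the dilution arises only if the wound-closure scan is used. But section 5.3 restricts the 6-week scan to patients with neurological injury, so the time-matched reading loses its comparison group.

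**Week 6 may be the intended target.** For a question about symptoms still present at 6 weeks, a recovered patient is correctly negative. That is fair. However, the protocol does not limit its hypothesis to persistent symptoms, and its motivating rates include temporary ones. Reproducing those rates is not a listed objective, so failing to do so is no fault.

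**The size is not documented.** It is tempting to read 21% dullness against the cited 8% chronic hypoesthesia as about 62% recovery (1 − 0.08/0.21). The documents do not support this: the two figures come from different series and different symptoms, the Introduction itself flags possible selection bias in the second, and chronic does not mean 6 weeks. Section 7 also states no hypothesis test, so p-values for the illustrative tables would have no counterpart in the plan.

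**Conclusion.** The concern holds in a limited form. No postoperative symptom or sensory assessment with the study instruments is scheduled before week 6, while the damage scan that every patient receives under section 5.3 is at wound closure and the rationale includes temporary symptoms. Symptoms that resolve in between are caught only incidentally. If the wound-closure scan is paired with week-6 symptoms, the association with postoperative symptoms is weakened.

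The size cannot be derived, because the protocol gives no time to resolution. Over an assumed range of 25% to 75% resolved, about 1 to 4 of roughly 5 expected dullness cases would be missed, which is material with so few events. The phi values are illustration only.

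The primary objectives (visualising the nerve, trocar distance, immediate damage) are untouched. What is affected is one secondary objective of an exploratory study, but it is the one that gives the ultrasound findings clinical meaning.

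**What to change.** 1. In section 5.3, give the existing Hypoesthesia questionnaire before discharge. A short dermatome check at the same time is optional, since it may need extra staff.
2. At the existing 6-week visit, ask whether numbness or pain of the lumbar region or abdominal wall occurred at any time since surgery and, if so, when it stopped.
3. In sections 2 and 5.2, state which scan is paired with which symptom time. Report the wound-closure scan against early or any symptoms, and separately against week-6 symptoms.
4. Reconcile the unconditional 6-week ultrasound in the Introduction and section 5.2 with the conditional one in section 5.3. As section 5.3 stands, that scan has no symptom-free comparison group.

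The first two changes cost a few minutes per patient (section 5.3 puts the questionnaire at 5 minutes) and need no extra visit. The drawbacks are recall error at 6 weeks and early pain that is hard to interpret because of wound pain and analgesics, so the early assessment should rely on numbness and sensation.

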# STUDY DESIGN

A explorative single-center prospective cohort study (n=25) at the Radboud University Medical Centre in Nijmegen.

# STUDY POPULATION

## Population (base)

Adult patients who undergo unilateral retroperitoneoscopic adrenalectomy, except patients with Cushing syndrome at the Radboud University Medical Centre. Patients will be approached at the outpatient clinic to obtain informed consent and participation in this study.

## Inclusion criteria

In order to be eligible to participate in this study, a subject must meet all of the following criteria:

- Age ≥18 years
- Obtained informed consent
- Surgery: unilateral retroperitoneoscopic adrenalectomy

## Exclusion criteria

A potential subject who meets any of the following criteria will be excluded from participation in this study:

- Patients with insufficient control of the Dutch language to fill out the questionnaires.
- Previous retroperitoneal surgery
- Preoperative (chronic) pain
- Preoperative medications: pain medication, anticonvulsants (e.g. pregabaline), antidepressants (e.g. amitriptyline)
- Cushing syndrome (less suitable patient population due to more bad quality fatty tissue and slow wound healing)

# METHODS

## Main study parameter/endpoints

- To assess postoperative nerve damage on ultrasound.
  - - Pre- and postoperative ultrasound to identify and measure the intercostal and subcostal nerves (precise location and cross sectional area (CSA) measurement)
- To measure the distances of the subcostal nerve to trocar positions.
  - - Postoperative measurement of distances (in mm) to trocar positions after marking of the nerve

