- Transversal position of probe, midaxillary line. Locating 10^th^, 11^th^ and 12^th^ rib.

- Locating tip 12^th^ rib, locating nerve latero-caudally (power doppler to verify adjacent blood vessel)

- Cross sectional area (CSA) measurement of subcostal nerve, marking the position on skin

- Following lateral / medial cutaneous nerve branches in surgical area, capturing and CSA measurement of abnormalities with note of localization with respect to midaxillary (vertical) and umbilical (horizontal) lines

Data management:

Given informed consent, filled out questionnaires, medical data extracted from electronic patient records are analyzed by [name] and stored in separate folders. Only [name] and HL (primary investigator) have insight in these data. Other authors in this study can view the data upon request. The data will be stored for 15 years.

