# STATISTICAL ANALYSIS

The principle investigator (HL) has final responsibility with regard to the data. Incidence of objective and subjective nerve damage will be expressed as absolute numbers and percentages. Distance from trocar to nerve will be expressed in absolute numbers.

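### Ultrasound nerve damage is a primary endpoint reported as an incidence, but the protocol states no criterion for damage, no replicate reading and no masking of the reader

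*Protocol*

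**What the plan says.** The first main endpoint in Protocol section 5.1 is "To assess postoperative nerve damage on ultrasound". The method under it is "Pre- and postoperative ultrasound to identify and measure the intercostal and subcostal nerves (precise location and cross sectional area (CSA) measurement").

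Section 5.3 sets out two theatre sessions. Before surgery, "an ultrasound is performed by a clinical neurophysiology research technician with measurement of the intercostal / subcostal nerve". After wound closure, "Then repeat measurement of intercostal / subcostal nerve is performed to assess nerve damage / oedema". The scan protocol in the same section asks for "Cross sectional area (CSA) measurement of subcostal nerve, marking the position on skin". It also asks the technician to follow the cutaneous branches, with "capturing and CSA measurement of abnormalities with note of localization". The closest the document comes to saying what damage is stands in the Introduction, which asks "if we can visualise nerve injuries by ultrasound (direct lesions, oedema").

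Section 5.3 blinds the surgeon to both sets of ultrasound results. It says nothing about masking the person who performs or reads the scans.

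Section 7 gives the summary measure: "Incidence of objective and subjective nerve damage will be expressed as absolute numbers and percentages". The table in section 7.1 lists ultrasound parameters as quantitative. Section 3 describes an exploratory single-centre cohort of 25 patients, without a comparison group.

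**The concern.** An incidence needs a yes or no for every patient. What is collected is a continuous CSA at two time points plus a visual impression, and nothing in the protocol turns these into a yes or no. It gives no CSA change that counts as damage, no criterion for a lesion or for oedema, no grading, and no rule for combining several nerves in one patient.

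Three features make this more than a missing detail:

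- The second theatre scan is done after wound closure, so whoever performs it knows that it is postoperative.
- There is no control group in which false positives would show up and could be subtracted. They go straight into the reported percentage.
- Whether the nerve can be visualised at all is part of the primary objective in section 2, so the precision of its CSA cannot be taken as known. No replicate reading is stated from which it could be estimated.

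The secondary aim of relating symptoms to ultrasound damage uses the same classification, so any misclassification carries over. What counts as a primary event belongs in the protocol. Replicate readings and saved images can be obtained only while patients are being scanned.

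**Working it through.** **There is no figure to reproduce.** The protocol gives n = 25 without a precision, power or effect-size calculation, and gives no measurement error for CSA.

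**What is fixed and what is open**

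- Endpoint and summary: fixed (sections 5.1 and 7).
- Sessions: one before surgery and one after wound closure (section 5.3). The number of readings per session is not stated.
- Kinds of injury: direct lesions, oedema and abnormalities are named (Introduction and section 5.3) but not defined.
- Masking: surgeon only (section 5.3).
- Images: nerve locations are photographed and abnormalities captured (section 5.3). Saving an image of every measured nerve is not stated, so a later masked re-read is not assured.

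**Illustration of what an unstated cut-off can do.** All of the following are assumptions: no true change, independent normal errors, one reading per session, a one-sided rule, rates per nerve, and a CV of 5% to 20% per reading.

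- SD of the pre-to-post difference = √2 × CV
- False-positive rate = 1 − Φ(cut-off / SD)

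For a rule of more than 20% increase:

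| CV per reading | SD of difference | 20% / SD | False-positive rate | Expected in 25 nerves |
|---|---|---|---|---|
| 5% | 7.1% | 2.83 | 0.2% | 0.1 |
| 10% | 14.1% | 1.41 | 7.9% | 2.0 |
| 15% | 21.2% | 0.94 | 17.3% | 4.3 |
| 20% | 28.3% | 0.71 | 24.0% | 6.0 |

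The cut-off matters as much as the CV. At a CV of 10%, a rule of more than 10% labels 24.0% of undamaged nerves, and a rule of more than 30% labels 1.7%.

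**Several nerves per patient.** Suppose a patient counts as damaged when either of two nerves is positive, with independent errors. The 7.9% per nerve then becomes 1 − (1 − 0.079)² = 15%.

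**Smallest detectable change.** With k readings averaged per session, this is 1.96 × CV × √(2/k).

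- One reading: 13.9%, 27.7%, 41.6% and 55.4% at CVs of 5%, 10%, 15% and 20%.
- Mean of two readings: 9.8%, 19.6%, 29.4% and 39.2%.

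A rule that counts a change in either direction beyond this limit has a 5% false-positive rate per nerve by construction. That is 0.05 × 25 = 1.25 expected labels at one nerve per patient, if the error is estimated correctly.

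**The case against.** The best defence is that the protocol describes a visual judgement supported by CSA, not a CSA threshold. In the scan protocol the technician follows the branches, finds an abnormality, and then measures it. Injury types are named. The equipment, preset, probe, depth, gain range, patient position and landmarks are all fixed, which should hold measurement error down. The study is exploratory with 25 patients, has no hypothesis test, and leaves any change of technique to the future. Learning what injury looks like on ultrasound is part of its aim. Section 7 does not name ultrasound when it speaks of objective damage, and section 7.1 already foresees quantitative reporting of ultrasound parameters.

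Much of this stands, and it rules out some stronger readings:

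- **That the headline percentage is mostly noise.** A reader might infer this from the illustration. The CV and the cut-off are assumed, and at a CV of 5% with a rule of more than 20% the false-positive rate is about 0.2%. The documents support neither a high nor a low figure.
- **That exactly one reading is taken per session.** The number is not stated. One is the natural inference, because no replicate is mentioned.
- **That no analysis plan could help.** A plan could define damage as a visible lesion only, or report CSA change only as a continuous quantity. What it cannot supply afterwards is a study-specific estimate of measurement error, or images that were not saved.

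The defence does not remove the central gap. If damage is a visual call, it has no criterion, and no masking of the person making it is stated. Ultrasound damage is a primary endpoint, so the natural reading of objective damage in section 7 includes it.

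**Conclusion.** The point holds as a gap in definition and measurement, and it should be corrected. As written, the primary percentage is set by an unmasked reader's judgement or by a cut-off chosen afterwards, in a study with no control group to show the false positives. Its size cannot be derived from the protocol. Under the stated assumptions, a rule of more than 20% CSA increase would mislabel between about 0.2% and 24% of undamaged nerves over a CV range of 5% to 20%. That range shows what is left open and does not predict the result. The exploratory purpose and the small sample lower the stakes, but they do not excuse a primary event without a definition.

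**What to change.** Amend sections 5.1 and 5.3 as follows.

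- **Replicates.** In both the preoperative and the postoperative theatre session, take two CSA readings per nerve, lifting the probe between them, and save all images.
- **Definition.** State in advance that damage is a visible lesion or loss of continuity, or a pre-to-post CSA change beyond the smallest detectable change estimated from those repeats. Note that repeats within a session may understate error between sessions, so the limit may be too small. State how several nerves in one patient are combined.
- **Masked re-trace.** Have the same technician re-trace the saved images later, with the time point masked as far as the images allow. Use that reading for the primary result.
- **Reporting.** Give the paired CSA change in mm² with a 95% confidence interval beside the incidence.

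The repeats should not be taken only at 6 weeks. Section 5.3 makes that scan conditional on neurological injury, so they would come from a selected subset. Section 5.2 lists the same scan without that condition, and the two sections need to be reconciled.

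The cost is protocol wording, slightly longer scanning under anaesthesia and some re-tracing time. No extra patients or staff are needed. The added scanning should be checked against the 10 minutes of longer anaesthesia estimated in section 8.3.
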